| Synopsis Dosage and Administration;
6.1.3. Linezolid/Placebo Therapy for
Ceftriaxone-resistant S. pneumoniae
and S. aureus | 
If the incidence of MRSA in CAP isolates is prevalent (ie, greater the 15%) in the local institution or region, or additional subject-specific risk factors are present, such as a history of prior MRSA infection or a surveillance culture positive for MRSA, linezolid/linezolid/placebo should be added to cover the possibility of <del>Staphylococcus aureus</del> (S. aureus) based on the presence of:...
 
If the incidence of MRSA in CAP isolates is not prevalent (ie, less than 15%) in the local institution or region, the investigator may wait for definitive confirmation of MRSA sensitive to linezolid in the respiratory specimen collected within 72 hours before randomization prior to adding linezolid/placebo.
 
Linezolid/placebo will be discontinued at <del>48</del>72 hours if S. aureus <del>or ceftriaxone-resistant pneumococcus</del> is not isolated from the baseline cultures.
 | 
Allows the option to wait for confirmed MRSA prior to adding linezolid in areas of the world where MRSA is not a common CAP pathogen.
 
Culture results are available in 48 hours or less so the time was reduced from 72 to 48 hours, per FDA request. Ceftriaxone resistant pneumococcus was removed for clarity.
 |

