## SYNOPSIS (CONTINUED)

In addition, 2 or more of the following criteria:

- Temperature >39°C
- Heart rate >140 per minute
- Respiratory rate >30 breaths per minute
- Hemoptysis
- Leukopenia
- Influenza symptoms within last 2 weeks (cough, coryza, fever)
- Necrotizing lesion(s) on chest X-ray or CT scan
- Known local case(s) of panton-valentine leukocidin (PVL) positive *S. aureus* infections

Linezolid/placebo will be discontinued at 48 hours if *S. aureus* is not isolated from the baseline cultures.

If the subject meets the criteria listed above but a Gram stain cannot be immediately obtained (i.e., the sputum sample is obtained at night), linezolid can be added empirically until the Gram stain results are available. If the results do not show gram-positive cocci in clusters from an adequate specimen, then treatment with linezolid should be discontinued.

If the incidence of MRSA in CAP isolates is not prevalent (i.e., less than 15%) in the local institution or region, the investigator may wait for definitive confirmation of MRSA sensitive to linezolid in the respiratory specimen collected within 72 hours before randomization prior to adding linezolid/placebo.

The following dosage of linezolid/placebo will be administered:

- Linezolid will be administered to those subjects randomized to ceftriaxone, at a dose of 600 mg in 300 mL of D5W every 12 hours by i.v. infusion over a period of 60 minutes. Placebo of 300 mL of normal saline (NaCl 0.9% solution) will be administered to those subjects randomized to ceftobiprole, at a volume of 300 mL every 12 hours by i.v. infusion over a period of 60 minutes. Normal saline (NaCl 0.9% solution) will replace D5W as the placebo solution for ceftobiprole in order to minimize the amount of free water delivered to subjects who are randomized to receive additional coverage with linezolid/placebo as follows:

| Ceftobiprole Arm                                               | Ceftriaxone Arm                                              |
|----------------------------------------------------------------|--------------------------------------------------------------|
| Placebo (50 mL D 5 W) every 24 hours                | Ceftriaxone (2g in 50 mL D 5 W) every 24 hours    |
| Ceftobiprole (500 mg in 250 mL D 5 W) every 8 hours | Placebo (250 mL normal saline ) every 8 hours)        |

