### **1.1.2. Comparator, Ancillary, and Oral Study Drugs**

#### **Comparator Study Drugs**

In this study, ceftobiprole will be compared with i.v. ceftriaxone with/without linezolid (comparator).

Ceftriaxone is a cephalosporin antibiotic that has been shown to be safe and efficacious in treating CAP and has good activity against the major bacterial pathogens including *S. pneumoniae*, *H. influenzae*, *S. aureus* (but not MRSA), and *K. pneumoniae*. Ceftriaxone is recommended in treatment guidelines for treating hospitalized patients with pneumonia. The most common side effects (incidence  $\geq 1\%$ ) of ceftriaxone are hematology disturbances (eosinophilia, thrombocytosis, and leukopenia), elevations of liver transaminases, diarrhea, rash, elevations of blood urea nitrogen (BUN), and irritation at the site of injection. Some less common side effects (incidence  $< 1\%$ ) of ceftriaxone are phlebitis at the i.v. site, pruritus, fever, chills, anemia (including hemolytic), neutropenia, thrombocytopenia, prolongation of prothrombin time, elevations of alkaline phosphatase and bilirubin, elevation of serum creatinine, urinary casts, headache, dizziness, vaginitis, diaphoresis, and flushing. Rare but serious side effects include anaphylaxis, seizures, renal failure, agranulocytosis, and pseudomembranous colitis.

Linezolid is an oxazolidinone antibiotic that has been shown to be safe and efficacious in treating CAP due to gram-positive pathogens including MRSA and PRSP. The most common side effects (incidence  $\geq 1\%$ ) of linezolid are diarrhea, headache, nausea, vomiting, insomnia, constipation, rash, dizziness, and fever. Some less common side effects (incidence  $< 1\%$ ) of linezolid include oral moniliasis, vaginal moniliasis, hypertension, dyspepsia, localized abdominal pain, pruritus, and tongue discoloration. Rare

but serious side effects include myelosuppression, optic or peripheral neuropathy, and pseudomembranous colitis.

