### **Rationale for Choice of Comparators and Oral Switch Therapy**

Ceftriaxone was chosen as the primary comparator in this study because it is a standard first-line therapy for subjects with CAP infections who require hospitalization. Ceftriaxone also has the same route of administration (i.v.) as ceftobiprole.

In order to allow subjects at-risk for MRSA to participate in the study, an additional drug with anti-MRSA activity will be added to ceftriaxone in subjects who meet specific inclusion criteria. Vancomycin, a glycopeptide, is effective against most strains of MRSA, but there are some strains of *S. aureus* with low-level resistance to vancomycin (VISA), and recently strains have been identified with high-level resistance to vancomycin

(VRSA). Linezolid, an oxazolidinone, has a narrow spectrum of activity with no useful gram-negative activity. It has been proven to be effective in treating MRSA infections and has in vitro activity against MRSA strains resistant to vancomycin. A recent analysis has suggested that linezolid may be superior to glycopeptides for the treatment of *S. aureus* pneumonia and it was therefore, chosen as part of the comparator regimen.

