#### **Anti-staphylococcal Therapy**

If the incidence of MRSA in CAP isolates is prevalent (i.e., greater than 15%) in the local institution or region, or additional subject-specific risk factors are present, such as a history of prior MRSA infection or a surveillance culture positive for MRSA, linezolid/placebo should be added to cover the possibility of *S. aureus* based on the presence of:

- Gram-stain from adequate sputum with gram-positive cocci in clusters as predominant organism (>10/hpf) or respiratory culture positive for *Staphylococcus* within 72 hours before randomization.

In addition, 2 or more of the following criteria:

- Temperature >39°C

---

\* This section of the protocol has been revised. Please refer to the section of this document entitled PROTOCOL AMENDMENTS (Amendment INT-3, 22 December 2006) for a detailed description of the specific changes.

- Heart rate >140 beats per minute
- Respiratory rate >30 breaths per minute
- Hemoptysis
- Leukopenia
- Influenza symptoms within last 2 weeks (cough, coryza, fever)
- Necrotizing lesion(s) on chest X-ray or CT scan
- Known local case(s) of PVLpositive *S. aureus* infections

Linezolid/placebo will be discontinued at 48 hours if *S. aureus* is not isolated from the baseline cultures.

If the subject meets the criteria listed above but a Gram stain cannot be immediately obtained (i.e., the sputum sample is obtained at night), linezolid can be added empirically until the Gram stain results are available. If the results do not show gram-positive cocci in clusters from an adequate specimen, then treatment with linezolid should be discontinued.

If the incidence of MRSA in CAP isolates is not prevalent (i.e., less than 15%) in the local institution or region, the investigator may wait for definitive confirmation of MRSA sensitive to linezolid in the respiratory specimen collected within 72 hours before randomization prior to adding linezolid/placebo.

The following dosage of linezolid/placebo will be administered:

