### **9.3.2. Microbiological Procedures and Efficacy Assessments**

Samples for appropriate culture (respiratory secretions and blood) must be obtained before the start of study therapy. Microbiological procedures will be done according to local practice. The sponsor will provide E-test® and Discs for susceptibility testing to ceftobiprole. Quantification or respiratory cultures should be recorded according to standard procedures of the local laboratory (see Attachment 3, Procedure for Collection, Culture, Susceptibility Testing, Storage, and Shipment of Microbiological Samples).

An aliquot of each potential pathogen isolated, including duplicate (follow-up) isolates from all assessments, will be shipped to the central laboratories for centralized antimicrobial susceptibility testing and pathogen identification, using Clinical and Laboratory Standards Institute (CLSI) methods. Sample handling and shipping will follow instructions provided by

the central laboratories. In cases where pathogens are characterized at the study center and centrally, the central laboratory data will be considered definitive.

The clinical investigator should be informed at the earliest occasion (overnight culture, 48-hour report) of suspected infection/colonization/superinfection with resistant pathogens.

The sponsor will provide the test kit for *L. pneumophila* urine antigen testing, which will be performed by the local laboratory.

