##### *Inoculum*

Sixteen to 18-hour colonies should be suspended in 0.85% saline to obtain a turbidity equivalent to 0.5 McFarland turbidity standard. This suspension will be swabbed on the agar plates 3 times, each time rotating the agar plate 60° completely covering the agar surface with inoculum.

E-test: Before placement of E-test strip, allow the inoculum to dry on agar surface for approximately 10 minutes.

DISK: Before placement of disk, allow the inoculum to dry on the agar surface for 3 to 5 minutes.

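### The option to wait for confirmed MRSA (Section 6.1.3 and Synopsis) depends only on local prevalence below 15%, so read literally it overlaps the rule to add linezolid/placebo for subjects with an MRSA risk factor

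*Protocol*

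**What the plan says.** Section 6.1.3 (Anti-staphylococcal Therapy) has two rules that bear on when linezolid/placebo starts. The Synopsis repeats both in nearly the same words.

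- **Adding rule.** Linezolid/placebo should be added if local MRSA prevalence in CAP isolates is above 15%, or if "additional subject-specific risk factors are present, such as a history of prior MRSA infection" (a positive MRSA surveillance culture is the other example given). Either trigger also needs a Gram-stain or respiratory culture finding and two or more of eight listed clinical criteria.
- **Waiting sentence.** If MRSA "is not prevalent (i.e., less than 15%) in the local institution or region, the investigator may wait for definitive confirmation of MRSA". The Synopsis wording is the same: "the investigator may wait for definitive confirmation of MRSA sensitive to linezolid". The only condition is prevalence.

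Three other places bear on intent. Section 3.2 explains why the drug is in the comparator regimen: "In order to allow subjects at-risk for MRSA to participate in the study, an additional drug with anti-MRSA activity will be added". Section 1.1.2 describes ceftriaxone's activity as including "S. aureus* (but not MRSA), and *K. pneumoniae". The rationale for Amendment INT-3, which introduced the waiting option, places it "in areas of the world where MRSA is not a common CAP pathogen". That is a regional reason and does not mention subject-level risk.

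**The concern.** The two rules use different conditions. The adding rule looks at the region or the subject; the waiting sentence looks at the region alone. A subject with prior MRSA infection, a positive Gram stain or culture and two or more criteria, enrolled where prevalence is low, is therefore told both that the drug should be added and that the investigator may wait. No sentence says which instruction takes precedence.

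What is at stake is subject safety in the comparator arm. Ceftobiprole is described in Section 1 as active against MRSA, so a waiting subject in that arm still has cover. A waiting subject in the comparator arm has ceftriaxone only. The investigator is blinded and cannot tell the two apart. Section 1.2 itself gives the high mortality of *S. aureus* pneumonia as the reason for having linezolid in the regimen.

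**Working it through.** The protocol gives no figure to reproduce here. The check is to write the two rules as conditions and see where they meet.

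Inputs, all from Section 6.1.3 and repeated in the Synopsis:

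- P = local MRSA prevalence in CAP isolates
- R = subject-specific MRSA risk factor present
- G = Gram-stain or culture finding met
- C = two or more of the eight clinical criteria met

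Rules:

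- Add = (P > 15% or R) and G and C
- Wait = P < 15%

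Taking P as 10%, 15% or 20% and each of R, G and C as yes or no gives 3 × 2 × 2 × 2 = 24 combinations. In 18 of them G or C is not met, so the adding rule does not apply and the two rules cannot conflict. The other 6 have both G and C met:

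| P | R | Add | Wait |
|---|---|---|---|
| 10% | no | no | yes |
| 10% | yes | **yes** | **yes** |
| 15% | no | no | no |
| 15% | yes | yes | no |
| 20% | no | yes | no |
| 20% | yes | yes | no |

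Exactly one combination meets both rules: low prevalence with a risk factor present. One combination meets neither: prevalence of exactly 15% with no risk factor.

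Which reading is natural? R is joined to P > 15% by *or*, so R changes the outcome only where P is 15% or less. If the waiting sentence overrode R whenever P < 15%, R would bind only at exactly 15%. A reading that leaves a clause with almost no work to do is unlikely to be the intended one. Section 3.2 and the regional rationale for the amendment point the same way.

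With the corrected condition, Wait = P ≤ 15% and not R. This is the exact complement of (P > 15% or R). When G and C are met, every subject then falls under one rule and only one: the 10%/yes row becomes add only, and the 15%/no row becomes wait only.

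**The case against.** The strongest reply is that the text already resolves itself. The specific rule says the drug should be added; the general sentence only permits waiting. Reading the permission as overriding the rule nearly empties the risk-factor trigger. Nothing obliges an unsafe act either: the investigator stays free to add linezolid/placebo at once. Subjects are seen daily in hospital, and Section 9.3.2 says of suspected resistant pathogens that the investigator "should be informed at the earliest occasion (overnight culture, 48-hour report"). Harm needs an investigator who knows of the risk factor, the stain or culture and the clinical criteria, and still relies on the permissive sentence.

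Most of this stands. The natural reading is to add, the affected group is narrow, and daily review limits the consequence. It does not remove the ambiguity. The waiting sentence carries no exception and is addressed to the person making the decision. A dosing rule in a multicenter trial should not depend on inference.

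The remark about exactly 15% is slight. The words for prevalent and not prevalent cover every case between them; only the figures in brackets leave the gap, and a risk-factor subject at 15% falls under the adding rule anyway. It is worth closing only because the same sentence is being edited.

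A reader might also infer that Sections 15.1 and 1.2 and the study diagram note in 3.1 are wrong because they describe linezolid without the conditions of 6.1.3. They are summary statements and need not repeat those conditions. No defect is shown there.

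**Conclusion.** The overlap is real as a matter of wording and appears in both places. It is a minor safety clarification, still worth making because the literal permission allows MRSA cover to be withheld from subjects who, by the same section, should receive it.

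Its size cannot be derived. The protocol gives no count of low-prevalence sites or of subjects with a risk factor who meet the other conditions.

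A reader might try to bound the delay, for instance by taking the 48-hour culture report as the limit and counting the 12-hourly linezolid doses missed. The documents do not support such a bound:

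- The specimen may be up to 72 hours old at randomization, so the result may already be at hand.
- Attachment 3 allows refrigerated transfer to the local laboratory within 24 hours.
- Confirmation must include linezolid sensitivity, and no timing for that test is given. The plate timings in Attachment 3 are for ceftobiprole.

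A reader might also infer damage to the stratified randomization or to the noninferiority comparison. That does not follow. Section 5.2 stratifies on need for anti-staphylococcal therapy as judged at enrollment; it does not fix when the drug starts. Nothing in the documents shows that a small, uncounted group would alter the primary conclusion.

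The point rests on one assumption: that some investigator could apply the waiting sentence as written, without reading the risk-factor trigger into it.

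**What to change.** In Section 6.1.3 and in the Synopsis, make two changes to the condition of the waiting sentence: set the prevalence figure to *15% or less*, and add *and no subject-specific MRSA risk factors are present*. The rest of the sentence stays as it is.

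This keeps the regional option for every subject without a risk factor, removes the overlap and closes the gap at exactly 15%. The stratification factor should be left unchanged.

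The cost is one clause in two places in the next amendment, with no change to the IVRS, strata, visits or data collection. The clinical downside is that a few more subjects start linezolid/placebo empirically. Section 6.1.3 already limits that by stopping it at 48 hours when *S. aureus* is not isolated from the baseline cultures.

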Target duration of study drug treatment (i.v. and oral) for all subjects will be a minimum of 5 days and a target of 7 days. If, in the investigator's opinion, a subject requires additional days of study therapy, the duration of the therapy may be extended (up to a maximum of 10 days). Subjects will be evaluated at Day 5 and 10 while on therapy.

Linezolid or placebo will be added as concomitant therapy based on initial signs and symptoms suggestive of MRSA or *S. aureus*. Linezolid or placebo should be discontinued once infection with MRSA or CRSP is ruled out.

Therapy can be further extended to a maximum of 14 days after approval by the sponsor's Medical Monitor. Subjects will be evaluated at Day 14 while on prolonged therapy.

Late Follow-up Visit is by telephone contact. Subjects reporting signs or symptoms consistent with pulmonary infection should be evaluated by a physician.

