### **6.1.3. Linezolid/Placebo Therapy for Ceftriaxone-resistant *S. Pneumoniae* and *S. Aureus*\***

#### **Antibiotic coverage of Ceftriaxone-resistant *S. pneumoniae* (CRSP)**

Linezolid or placebo should be added to study treatment for subjects with confirmed CRSP provided the sensitivity of the isolate to linezolid has been confirmed.

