### **Blood Cultures**

At least 2 sets of aerobic/anaerobic blood cultures must be obtained according to local practice for each subject, within 24 hours before the start of treatment. In the event that a subject has received nonstudy antibiotics before study enrollment, blood cultures obtained before, or as soon as possible, but within 24 hours after the start of nonstudy antibiotic treatment must be available. These cultures must be repeated, if necessary, so that a blood culture is collected within 24 hours before the first dose of study drug. At least 1 culture should be taken from a peripheral vein. Cultures must either be drawn one after the other from different sites or drawn from the same site, 10 minutes apart. Any potential pathogen should be stored and shipped to the central laboratory.

Positive blood cultures at baseline or follow-up (concordant growth of the same pathogen in at least 2 bottles or corresponding to a respiratory isolate) must be repeated at each visit or more frequently, if indicated, until negative cultures are obtained. If blood cultures on 3 consecutive days are positive, the subject should be withdrawn from the study and considered a treatment failure. If negative blood cultures are obtained at baseline, blood cultures should be repeated at subsequent visits only if clinically indicated. Culture procedures will be according to local practice.

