## 15. ETHICAL ASPECTS

### 15.1. Study-Specific Design Considerations

There are 5 aspects of this study design requiring ethical justification.

Surveillance studies of susceptibility patterns of microorganisms known to cause CAP suggest that both study regimens (ceftobiprole/placebo or ceftriaxone/linezolid) should be highly efficacious in treating such infections. The comparator regimen consists of approved antibiotics. Ceftriaxone is commonly recommended to treat CAP. Linezolid is included initially to provide treatment for resistant pathogens (e.g., PRSP, MRSA) that are included in the spectrum of activity of ceftobiprole. Once these resistant pathogens are ruled out as the cause for CAP, the linezolid will be discontinued in order to decrease exposure of subjects to unnecessary antibiotics. However neither treatment regimen is active against *Legionella* spp, which are uncommon causes of CAP but have the potential to cause severe, even fatal disease. An overwhelming number of cases of CAP due to *Legionella* spp are caused by *L. pneumophila*. The protocol excludes subjects with CAP known or suspected to be caused by *Legionella* spp and mandates a urine test for legionella antigen that is highly specific and sensitive.

The second issue is the selected dose of ceftobiprole. The PK modeling data of ceftobiprole suggest that the current dosing regimen should be highly efficacious in treating CAP due to *S. pneumoniae* (including penicillin and ceftriaxone-resistant strains), *S. aureus* (including MRSA and VRSA), *H. influenzae*, and the majority of strains of enteric gram-negative rods (e.g., *K. pneumoniae*).

The third issue is that there are no efficacy data in the use of ceftobiprole for treatment of pulmonary infections or infections due to *S. pneumoniae*. The only data in subjects is from the Phase 2 studies in complicated skin infections and used a different dose of ceftobiprole. However, in vitro and animal studies of ceftobiprole demonstrate that it behaves in a similar fashion to other cephalosporins. Cephalosporins have been used as first line therapy for CAP for over 2 decades and it is anticipated that ceftobiprole will be equally efficacious. Additionally, an IDMC will assess the efficacy data in an ongoing fashion. The same IDMC will also review efficacy data from the 2 ongoing Phase 3 studies in nosocomial pneumonia.

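### Section 6.1.3 has no rule adding linezolid/placebo on confirmed MRSA alone, so a few comparator subjects with known MRSA could stay on ceftriaxone only

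*Protocol*

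**What the plan says.** Section 6.1.3, repeated in the Synopsis, sets the rules for adding linezolid (comparator arm) or its placebo (ceftobiprole arm).

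- **CRSP.** "Linezolid or placebo should be added to study treatment for subjects with confirmed CRSP", on the single condition that the isolate has been shown sensitive to linezolid.
- **MRSA prevalence above 15%, or subject-specific risk factors.** Linezolid/placebo should be added on a sputum Gram stain with clusters or a respiratory culture positive for Staphylococcus. The rule then continues: "In addition, 2 or more of the following criteria". Eight criteria follow.
- **MRSA prevalence below 15%.** The treating site "may wait for definitive confirmation of MRSA sensitive to linezolid in the respiratory specimen collected within 72 hours before randomization prior to adding linezolid/placebo".
- **Empiric start while a Gram stain is pending.** "If the results do not show gram-positive cocci in clusters from an adequate specimen, then treatment with linezolid should be discontinued".
- **48-hour stop.** Linezolid/placebo ends if no *S. aureus* has grown from the baseline cultures.

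On blood, Section 9.3.3 states: "At least 2 sets of aerobic/anaerobic blood cultures must be obtained according to local practice for each subject". Section 1.1.2 describes ceftriaxone as active against *S. aureus* but not MRSA. Section 15.1 gives the purpose of the added drug: "Linezolid is included initially to provide treatment for resistant pathogens (e.g., PRSP, MRSA) that are included in the spectrum of activity of ceftobiprole".

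**The concern.** The clearest reason to give linezolid for MRSA is a confirmed isolate, yet the protocol does not make confirmation sufficient. The rule above 15% is written for empiric treatment and keeps its clinical criteria even when a culture result is in hand. As a result, confirmed respiratory MRSA has a more direct route to linezolid at a low-prevalence site than at a high-prevalence one.

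At stake is treatment of a dangerous infection. Section 1.2 justifies linezolid in the comparator by the high mortality of *S. aureus* pneumonia. A comparator subject who falls into the gap receives no drug active against the known pathogen, while a ceftobiprole subject in the same position does. Other antibacterials are not a permitted remedy: Section 4.4 prohibits nonstudy antibacterials until after late follow-up, and Section 8 bars other systemic antibacterial treatment.

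**Working it through.** No formula decides this point. The check reads the adding rules as a decision table for a subject with confirmed, linezolid-sensitive MRSA.

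1. **Site above 15% or subject risk factor; respiratory isolate from the 72 hours before randomization; two or more criteria.** Covered: the isolate satisfies the culture condition.
2. **Site above 15%; respiratory isolate; none or one criterion.** No rule adds linezolid/placebo.
3. **Site below 15%; respiratory isolate.** Adding is implied, since permission to wait for confirmation makes sense only if confirmation leads to treatment. No sentence says that it should be added.
4. **Any site; MRSA in blood only.** No rule acts on the blood result. The subject qualifies only if the sputum Gram stain independently shows clusters, two or more criteria are met, and the site is above 15% or a risk factor is present.
5. **For contrast, confirmed linezolid-sensitive CRSP.** Covered, with no condition on prevalence, specimen or clinical criteria.

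The gap is therefore rows 2 and 4. Other places where it might have been closed:

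- The notes to the design diagram in Section 3.1 base adding on initial signs and symptoms. Their only culture-related instruction concerns stopping: "Linezolid or placebo should be discontinued once infection with MRSA or CRSP is ruled out".
- Section 9.3.2 requires communication but names no action: "The clinical investigator should be informed at the earliest occasion (overnight culture, 48-hour report) of suspected infection/colonization/superinfection with resistant pathogens".
- The laboratory table in Attachment 3 attaches an investigator action to *Legionella*, ESBL producers, *Proteus vulgaris* and resistant nonfermenters. MRSA is not listed.
- Section 15.1 states a purpose, not a trigger.

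**Scale only.** The protocol gives no expected MRSA rate, no share of subjects at sites above 15% and no distribution of the criteria, so the number in rows 2 and 4 cannot be computed. What can be shown is what one subject weighs, using Section 11.1.

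- Per arm: 670/2 = 335 (ITT) and 266 (CE).
- One comparator subject moving from cure to failure: 100/335 = 0.30 points (ITT); 100/266 = 0.38 points (CE).
- 95% half-width at 90% cure in both arms: 1.96 × √(2 × 0.9 × 0.1/335) = 4.54 points (ITT); 1.96 × √(2 × 0.9 × 0.1/266) = 5.10 points (CE).
- Subjects needed to move the difference by more than 1 point: 4 in ITT (4/335 = 1.19 points), 3 in CE (3/266 = 1.13 points).

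These figures follow from the sample size alone and say nothing about how many subjects fall in the gap.

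**The case against.** The strongest reply is that the intent is plain. Permission to wait for confirmation presupposes treatment afterwards, linezolid stops only once MRSA or CRSP is ruled out, and Section 15.1 says why the drug is there. Nothing suggests that sites with more MRSA should respond less to a confirmed isolate. Several criteria are also easily met, such as recent influenza symptoms or known local PVL-positive cases. An investigator can contact the sponsor about a departure (Section 16.1) or stop treatment for safety (Section 10.2). All of this stands and makes the gap narrow. It does not close it: the conjunctive rule is explicit, and a foreseeable, serious case is left to decisions that may differ between sites.

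Three stronger readings might be inferred, and the protocol does not support them.

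- *The CRSP trigger is unconditional.* It is not; sensitivity to linezolid must be confirmed.
- *High-prevalence sites have no route at all for confirmed MRSA.* Respiratory MRSA with two or more criteria is covered.
- *The Gram-stain stop takes linezolid from subjects with known MRSA.* That sentence concerns empiric starts while a stain is pending. A subject whose pre-randomization respiratory culture is already positive meets the microbiological condition by culture. Harm would need the MRSA report to arrive before the delayed stain, so the point is marginal.

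Blood is also not ignored entirely. The 48-hour stop refers to baseline cultures in general, so *S. aureus* in blood prevents that stop in a subject already started. Under Section 9.3.3, positive blood cultures on three consecutive days lead to withdrawal and classification as a treatment failure. Neither provision starts linezolid.

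**Conclusion.** The point holds in a limited form. No rule makes confirmed MRSA sufficient by itself. The uncovered cases are respiratory MRSA with fewer than two criteria at sites above 15%, and MRSA found only in blood at any site. The protocol is silent on these cases; it does not forbid linezolid/placebo.

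The subjects affected are probably few, but the consequence for each could be serious. That makes this a matter of safety and comparator adequacy, and it should be corrected.

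A reader might go further and infer that the noninferiority result is materially biased. The protocol does not support that. If affected comparator subjects failed treatment, the shift would favor ceftobiprole, because only the comparator lacks cover. Its size cannot be derived and is probably small. The conclusion assumes that the rules are followed literally; investigators acting on the evident intent would shrink the gap further.

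**What to change.** Add one sentence to Section 6.1.3 and the Synopsis, parallel to the CRSP rule: *linezolid/placebo should be added for every subject in whom MRSA is confirmed from a valid baseline respiratory specimen or a baseline blood culture, once the isolate has tested sensitive to linezolid, whatever the local prevalence and however many clinical criteria are met.* The option to wait for confirmation at low-prevalence sites can stay.

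The words on a valid specimen matter. Sections 9.3.3 and 9.3.4 and Attachment 3 already separate valid from invalid samples, and MRSA from inadequate sputum should not trigger treatment by itself.

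The cost is one sentence in an amendment. Randomization, analysis and sample size are unchanged. Adding the drug after enrollment is already provided for with CRSP and at low-prevalence sites, and the placebo infusion in the ceftobiprole arm keeps the blind. The downside is slightly more linezolid exposure, possibly including some colonized subjects, which runs somewhat against the aim in Section 15.1 of limiting unnecessary antibiotics.
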